**5.2 Sniffin’ Sticks**

We will use the Sniffin’ Sticks to test the olfactory function. This test is part of regular clinical practice at the UMCU and is validated in healthy Dutch adults (31). The Sniffin’ Sticks are pen-like devices, which are filled with liquids containing different odours. We will use 12 different odours. For testing, the researcher will firstly remove the cap of the pen-like device. Secondly the researcher will place the pens tip 2 cm in front of the nostrils for 3 seconds. After 3 seconds the patient has to identify the odour. The interval between the presentations of the different odours will be at least 30 seconds to prevent olfactory desensitization (32). The patient will undergo this test preoperatively and 1 week postoperatively. With this information it will be possible to conclude whether the olfactory function is intact or not. We will test the olfactory function, because the perception of flavour is generated by taste and smell sensation (33). Some studies concluded that smell sensation plays a more dominant role in the tasting of food than taste function (34). The Sniffin’ Sticks will also be ordered from Burghart Messtechnik (Germany).

**5.3 Macronutrient and Taste Preference Ranking Task**

We will use the MTPRT to test the food preference in patients. The test consists of pictures of products from four macronutrient categories. These four macronutrient categories are high-carbohydrate, high-fat, high-protein and low-energy. The MTPRT consists of three parts: practicing, liking and ranking. During the practicing part four combinations of four pictures are presented and patients will be asked to rank these pictures according to ‘what they most desire to eat at that moment’. During the liking part 32 pictures of products are presented with the question ‘How much do you like [product name]?’. Patients will be asked to rate this question on a 100-point visual analogue scale anchored by ‘do not like at all’ and ‘like extremely’. During the ranking part patients will be asked to rank according to ‘what they most desire to eat at that moment’. Participant will first click on the product they most desire to eat at the moment of completing the task. Afterwards they will click on the second most desired product, followed by the third most desired product and the product they least desired to eat at the moment of completing the task. Patients will be asked to refrain from eating and to drink only water or tea without sugar during the three hours prior to the test session (35). The patient will undergo this test preoperatively, 1 week, 6 weeks postoperatively and 6 months postoperatively.

# 5.4 Electrogustometer

We will use the CE marked EGM to investigate the taste ability. Different studies have established that the EGM is a good clinical tool for measuring taste detection thresholds (23–25). Electric taste, tastes like metal and sour, will be assessed with the Electrogustometer SI-03 (Sensonics Inc., Haddon Heights, NJ). We will detect the electric taste threshold with anodal stimulation. We will stimulate from 0.25 to 450 uA using the forced-choice single staircase test procedure. The EGM manual describes the two-down one-up forced-choice single staircase procedure (see appendix 1). This taste threshold setting procedure has a correct response level of 70.7% (26,27). The stimulus duration will be set at 0.5 sec. The lowest number of uA that generates an electric taste will be determined to be the value of the taste threshold of the CTN. We will measure the taste detection threshold on the anterior and lateral region of both sides of the tongue, so we can compare the taste thresholds of the ipsilateral side of the tongue to the operated ear with the contralateral side of the tongue (see figure 1). The patient will undergo this test preoperatively, 1 week, 6 weeks and 6 months postoperatively.

[figure not shown]

Figure 2. Anterior tongue regions: anterior tongue (regions 5 and 6), lateral tongue (regions 2,3,4,7,8 and 9), central tongue (regions 11,12,13,14,15 and 16) and posterior tongue (regions 1 and 10) (28).

Different studies have established that EGM is a good clinical tool for measuring taste detection thresholds (23–25). The EGM can also assess regional taste thresholds. Sensitivity of detection is lower on the ipsilateral side of the tongue to CTN transection compared to the contralateral side of the tongue. We will measure the taste threshold of the lateral sides of the tongue (see figure 2). (29). Stimulus duration affects the threshold values and therefore the stimulus duration will be set at 0.5 sec. for all participants (28).

## No potential risks are described in the literature. The EGM doesn’t connect to any outside voltage source and uses a series of AA batteries to produce it’s stimuli. In addition, the amount of current is confined to very low uA levels (0.25-450 uA) that are detected primarily by taste afferents. By using a dual electrode, no current flows through the body. Patients with a pacemaker could therefore be included in the study, but as a precaution we will exclude these patients. The EGM manual describes the precautions for proper use of the EGM (see appendix 1).

# 6. METHODS

## 6.1 Study parameters/endpoints

### 6.1.1 Main study parameter

The main study parameter will be the 6 weeks postoperative amount of identified taste strips of the ipsilateral tongue of the operated ear. The range for possible scores is 0 to 20

### 6.1.2 Secondary study parameters

- The difference between the preoperative and postoperative EGM thresholds in uA for different locations of the tongue
- The difference between the preoperative and postoperative amount of identified sweet taste strips of the ipsilateral tongue of the operated ear
- The difference between the preoperative and postoperative amount of identified salty taste strips of the ipsilateral tongue of the operated ear
- The difference between the preoperative and postoperative amount of identified sour taste strips of the ipsilateral tongue of the operated ear
- The difference between the preoperative and postoperative amount of identified bitter taste strips of the ipsilateral tongue of the operated ear
- The difference between the preoperative and postoperative amount of identified umami taste strips of the ipsilateral tongue of the operated ear
- The postoperative existence of metallic taste sensation
- The postoperative existence of dryness of the mouth
- The postoperative existence of tingling sensations of the tongue
- The postoperative existence of numbness of the tongue
- The difference between the preoperative and postoperative score of the AHSP questionnaire
- The difference between the preoperative and postoperative score of the health-related quality of life questionnaire
- The difference between the preoperative and postoperative total and sub scores of the MTPRT
- The difference between the preoperative and postoperative odour identification score

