# 2. OBJECTIVES

Primary Objective:

To evaluate the effect of CTN injury on postoperative taste function measured using taste strips in patients undergoing primary stapes surgery or primary cochlear implantation.

Secondary Objective(s):

- To compare the postoperative taste function of sweet, sour, bitter, salty and umami measured using taste strips in patients between two types of CTN injury (stretching or sacrificing)
- To compare the postoperative EGM threshold in uA for different locations of the tongue in patients between two types of CTN injury (stretching or sacrificing)
- To compare the presence of postoperative symptoms of taste disturbance in patients between two types of CTN injury (stretching or sacrificing).
- To compare the postoperative perception of appetite, hunger and sensory in patients between two types of CTN injury (stretching or sacrificing).
- To compare the postoperative quality of life in patients between two types of CTN injury (stretching or sacrificing).
- To compare the postoperative enjoyment of food in patients between two types of CTN injury (stretching or sacrificing).
- To compare the postoperative food preference in patients between two types of CTN injury (stretching or sacrificing).
- To compare the postoperative odour identification score in patients between two types of CTN injury (stretching or sacrificing)

Other parameters:

- Age
- Gender
- Medical history
- Details of the stapes surgery or cochlear implantation

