# 8. STATISTICAL ANALYSIS

## All statistical analyses will be performed using the IBM SPSS Statistics version 21.0 software package (Chicago, Illinois, USA). A test for normality and histograms will be used to assess whether variables are normally distributed. We expect limited missing data. Potentially missing variables will be handled with multiple imputation.

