## 8.2 Secondary study parameters

EGM thresholds and the MTPRT will be reported preoperatively and 1 week, 6 weeks and 6 months postoperatively. The total score and scores of different categories of the questionnaires will be reported preoperatively and 1 week, 6 weeks, 3 months and 6 months postoperatively. The odour identification score will be reported preoperatively and 1 week postoperatively. Mean (or median) and standard deviation (or the range) will be reported. Differences between the different groups of CTN injury will be analysed using linear regression analysis.

Postoperative symptoms of taste disturbance will be analysed using logistic regression analysis, as these outcomes will be presented dichotomously.

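### The electrogustometry outcome is specified in raw microamperes and analysed by linear regression over an 1800-fold stimulus range, and Section 5.4 describes its threshold in two ways that need reconciling

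*Protocol*

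**What the plan says.** The unit is written into both places that define the outcome. The objective in Section 2 is "To compare the postoperative EGM threshold in uA for different locations of the tongue in patients between two types of CTN injury (stretching or sacrificing"). The parameter in Section 6.1.2 is "The difference between the preoperative and postoperative EGM thresholds in uA for different locations of the tongue". One names the postoperative value and the other a change, but both are in microamperes.

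Section 8.2 lists EGM thresholds with the other continuous secondary outcomes and continues: "Differences between the different groups of CTN injury will be analysed using linear regression analysis". It mentions no transformation. Section 8 adds "A test for normality and histograms will be used to assess whether variables are normally distributed", without saying what follows if they are not.

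On measurement, Section 5.4 says "We will stimulate from 0.25 to 450 uA using the forced-choice single staircase test procedure", cites the manual ("The EGM manual describes the two-down one-up forced-choice single staircase procedure (see appendix 1"), and adds "This taste threshold setting procedure has a correct response level of 70.7% (26,27"). It then defines the result: "The lowest number of uA that generates an electric taste will be determined to be the value of the taste threshold of the CTN". The protocol does not say which value a patient receives who does not respond at 450 uA.

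**The concern.** A stimulus range this wide is naturally read in ratios, because a patient whose threshold doubles has lost the same proportion of sensitivity wherever the threshold started. Least squares in microamperes weights that loss by its starting point. Variation at the insensitive end then tends to set the residual variance, and the group contrast is estimated less precisely. A mean difference in uA is also hard to interpret when one unit means something different at each end of the scale.

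The upper limit adds a second difficulty. A side that does not respond at 450 uA has a threshold known only to exceed 450. Section 5.4 itself notes reduced sensitivity on the side of a sectioned nerve, so such values are likeliest in one of the groups being compared.

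The third difficulty is the definition of the threshold. A forced-choice staircase estimates the current giving a set proportion of correct answers. The lowest current that evokes a taste is a different quantity, and single correct answers at low current can be guesses. If only that lowest level is written down, the staircase estimate may not be recoverable at analysis.

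**Working it through.** **1. The plan's own figure.** A two-down one-up staircase settles where two correct answers in a row have probability one half: p² = 0.5, so p = √0.5 = 0.707. The stated 70.7% is reproduced.

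**2. Width of the scale** (limits from Section 5.4).
- Ratio: 450 / 0.25 = 1800.
- log10(1800) = 3.26 log units; 20 × log10(1800) = 65 dB; log2(1800) = 10.8 doublings.

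**3. Weight of equal proportional changes.**
- 4 to 8 uA: raw change 4, log10 change 0.301.
- 225 to 450 uA: raw change 225, log10 change 0.301.
- Ratio of raw weights: 225 / 4 = 56.

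**4. Illustrative cost of the scale alone.** The protocol gives no EGM mean, SD or ceiling rate, so everything in this step is assumed except the stimulus limits and the 140 evaluable patients (14 degrees of freedom × 10, Section 4.4). The other inputs are:
- two equal groups;
- log-normal thresholds clipped to 0.25-450 uA;
- log10 SD of the change 0.35;
- a common postoperative shift of 0.1 log10 and a further 0.2 log10 in one group.

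A two-sample t-test of raw change is compared with one of log10 change, 3000 runs per row. The residual column is the share of the raw-scale residual sum of squares carried by the 7 most extreme of 140 patients (5%).

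| Baseline median (uA) | log10 SD | Power, raw | Power, log | Residual share | Postoperative values at 450 uA |
|---|---|---|---|---|---|
| 8 | 0.3 | 0.63 | 0.91 | 70% | 0% |
| 8 | 0.5 | 0.47 | 0.93 | 77% | 1% |
| 8 | 0.7 | 0.43 | 0.92 | 73% | 3% |
| 20 | 0.3 | 0.67 | 0.92 | 65% | 1% |
| 20 | 0.5 | 0.58 | 0.92 | 61% | 3% |
| 20 | 0.7 | 0.55 | 0.90 | 56% | 7% |
| 60 | 0.3 | 0.81 | 0.91 | 35% | 8% |
| 60 | 0.5 | 0.73 | 0.88 | 37% | 14% |
| 60 | 0.7 | 0.63 | 0.84 | 41% | 20% |

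The gap runs from 10 to 49 percentage points. With no effect (median 20, SD 0.5) the rejection rate was 0.043 raw and 0.044 log, so the test is not invalid on either scale.

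**5. Scale versus baseline adjustment.** A second assumed setting has 70 against 28 patients, a difference of 0.3 log10, SD 0.5, baseline 10 uA and pre/post correlation 0.5:

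| | Change score | Baseline as covariate |
|---|---|---|
| Raw uA | 0.68 | 0.69 |
| log10 uA | 0.74 | 0.85 |

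The whole step is 0.85 − 0.68 = 17 points. Taking logs of the change score gives 6 of them, and adding the baseline covariate on the log scale gives the other 11. The gain therefore belongs to the two changes together.

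**6. The two thresholds.** Section 5.4 names a 70.7% point and a lowest perceived current. In simulated staircases (7 reversals, steps of 0.1 and 0.2 log10, both assumed) the lowest correctly identified level lay 0.10 to 0.21 log10 below the mean of the reversals. That is a factor of 10^(−0.10) = 0.79 to 10^(−0.21) = 0.62. Its SD was 0.13-0.25 against 0.10-0.20. If the sentence is taken literally, the two definitions do not give the same number.

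**The case against.** The strongest reply is that the regression scale is not literally fixed. Section 8.2 has one generic sentence for several outcomes, and regressing a log threshold would satisfy it. Section 8 foresees a normality check, and acting on a failed check is not excluded. Transformation and ceiling handling are often left to a statistical analysis plan, which may exist. This stands in part: a reader should not infer that the raw difference is settled as the dependent variable, or that the normality check can change only the summary statistics. But Sections 2 and 6.1.2 both state the unit and Section 8.2 states the model, so the protocol as written points to a poor scale rather than being silent.

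A reader might also infer that non-responders are mis-scored. The protocol does not support that, because it gives no scoring rule for them at all. Nor does it show that a few insensitive patients will dominate the result. That is plausible on an 1800-fold scale but depends on an unstated distribution.

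The simulations favour the log scale by construction, since the data are generated log-normal with a proportional effect.

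On the threshold, the manual in appendix 1 is not at hand, and the sentence about the lowest current may be a loose gloss on the staircase result. That is a reason to reconcile the two statements, not to assume that a minimum over single trials is being recorded.

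**Conclusion.** The point holds in a limited form. The 1800-fold range and the 56-fold difference in weight follow from the protocol's own limits. A loss of precision and interpretability from linear regression in raw uA is likely. Its size is not known: the 10 to 49 point power gap and the 35-77% residual share rest on assumed medians, SDs and effects, and part of the gain available from the full remedy comes from baseline adjustment.

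It would be wrong to read this as an inflated false-positive rate, since the null setting gave about 4% on both scales. The missing rule for 450 uA is a gap to close, not a demonstrated error. The two threshold descriptions in Section 5.4 differ as written and must be reconciled.

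EGM is a secondary outcome. The primary taste-strip analysis and N = 154 are unaffected. The change is worth making but is not critical.

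**What to change.** - **Sections 2, 6.1.2 and 8.2:** analyse the postoperative log10(uA) threshold (or dB) by linear regression on injury group, with the preoperative log threshold as covariate, and report ratios. With the baseline in the model, the injury coefficient is the same whether the outcome is the postoperative value or the change, so this also removes the difference between Sections 2 and 6.1.2.
- **No response at 450 uA:** record it as such. In a sensitivity analysis, treat it as right-censored or rank it above all observed values. Do not pass it to multiple imputation as missing, because the imputation would not know that the value exceeds 450.
- **Section 5.4:** reconcile the two threshold statements with the EGM manual, so that one staircase-based estimate is defined and recorded for every site and visit.

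The cost is small: amended wording, a less familiar scale for readers, and the need to record the staircase estimate. No extra testing is needed. If the case report form does not already hold that estimate, it needs a field, which under Section 10.1 goes with a protocol amendment.

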### 6.1.3 Other study parameters

Baseline characteristics (age, gender), medical history and details concerning the surgical procedure that was performed.

## 6.2 Randomisation, blinding and treatment allocation

There will be no randomization. The patient and outcome assessor are blinded to the predictor variables, including the presence or absence of CTN injury. The surgeon will complete an electronic Case Report Form (eCRF) in Castor, including the predictor variable CTNinjury. Both patients and researchers will not be informed about the CTN injury until the patient has finished all evaluations. The eCRF will be locked to read for the researchers and the surgeon will not report the CTN injury in the surgery report. After a patient has completed all evaluations, the investigator will read the eCRF and report the CTN injury in the electronic patient record. We do not expect that there are circumstances that require us to unblind the patient or the outcome assessor during the study.

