A recently published systematic review of the effect of CTN injury during noninflammatory middle ear surgery concluded that patients with a stretched CTN were slightly more symptomatic than patients with a sacrificed CTN. The included studies were characterized by several limitations in their study design. The follow-up duration varied greatly between the included studies with a range of 6 weeks to 99 months. A longer follow-up duration may result in fewer symptoms due to the longer recovery time or habituation of symptoms (1). Secondly, age seems to be associated with recovery rate. Younger patients seem to have significantly higher recovery rates of CTN function compared to older patients (11). Most of the included studies disregarded age. Thirdly, postoperative taste dysfunction may have been underreported. It is not clear whether surgeon routinely asked their patients about taste dysfunction in the included studies. Lastly, most studies did not include quality of life as an outcome measure and therefore it remains unclear whether taste dysfunction significantly impacts quality of life (1).

*Purpose of this study*

A lack of high quality studies on the subject precludes firm evidence-based recommendations and demonstrates the need for a high-quality study. In order to accommodate this need, in the proposed double-blind prospective study we will investigate the effect of CTN injury on postoperative taste disturbance and quality of life.

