## 8.4 Interim analysis

No interim analyses will be performed.

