Only research members directly involved in this study will get access to the all of the collected in Castor. The clinical database will be supplemented with the outcome of three questionnaires (please see paragraph 7.3 Study Procedures). At the end of the study, all generated (meta)data will be stored as a proprietary format (.sav / .xlsx format) in a secure Research Folder Structure with access control. Only members of the research team who are directly involved in the study are allowed to access the key-linking table to enable patient re-identification (only for UMCU patients). In order to reproduce the study findings and to help future users to understand and reuse the (meta)data, all changes made to the raw data, including analysis steps will be documented in an analysis plan. Thus the secure research folder will serve at the end of the study as a data package. The data package will be locally archived on the secured research network disc of the division for 15 years after the study has ended. More details, including the state of FAIRness, can be found in our datamanagement plan on [https://dmponline.dcc.ac.uk/plans/71095](https://dmponline.dcc.ac.uk/plans/__.).

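### Section 6.2 lifts the blind to nerve injury one patient at a time, and nothing keeps the injury data closed to testers and analysts until the study ends

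*Protocol*

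**What the plan says.** Section 1 presents the work as blinded on both sides: "in the proposed double-blind prospective study we will investigate the effect of CTN injury on postoperative taste disturbance and quality of life". Section 6.2 states who is blind: "The patient and outcome assessor are blinded to the predictor variables, including the presence or absence of CTN injury". It protects this as follows: "The eCRF will be locked to read for the researchers and the surgeon will not report the CTN injury in the surgery report".

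The same section then says when the protection stops. It stops with each patient: "Both patients and researchers will not be informed about the CTN injury until the patient has finished all evaluations", and "After a patient has completed all evaluations, the investigator will read the eCRF and report the CTN injury in the electronic patient record". Section 6.2 also expects no need to unblind the patient or the outcome assessor while the study runs.

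Section 6.3 places the last test session at 6 months after surgery. Section 8.4 states: "No interim analyses will be performed".

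Section 10.1 describes data access. Castor access is by assigned role, but no role is defined for the injury item. Research team members extract clinical data from the electronic patient record. A general sentence adds: "Only research members directly involved in this study will get access to the all of the collected in Castor". It makes no exception for the surgeon's form.

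**The concern.** In a blinded study the exposure is usually kept from those who measure and analyse until measurement is over for everyone. Here the release is tied to the individual patient's last visit, so disclosure and testing run side by side for much of the study.

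The protocol does not keep the roles apart. Section 6.2 has the investigator read the form. Section 9.2 has the investigator sign the consent form with the patient, with the first test session on the same day. Sections 5.1 and 5.2 have the researcher run the taste strip and odour tests. These may be different people, but nothing requires it, and nothing keeps the unblinded investigator out of data preparation or analysis.

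Two things are at stake. First, someone who has learned how finished patients with each type of injury scored may carry that expectation into later face-to-face sessions. Second, choices that the protocol leaves unsettled could be made with exposure-specific results known. Section 6.1.1 makes the 6-week score the main parameter, while section 8.1 makes it the change from before surgery to 6-8 weeks. Section 3 has three injury categories, while the secondary objectives in section 2 compare two. A separate analysis plan was not available and may settle these points.

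**Working it through.** **Inputs from the protocol**
- Section 4.4: 80 stapes and 100 cochlear implant operations per year, 70% participation, 154 patients, 15 months.
- Section 6.3: last evaluation 6 months after surgery, primary assessment at 6 weeks (42 / 30.44 = 1.38 months).

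**Assumptions**
- Accrual is even and nobody withdraws.
- The form is read as soon as a patient finishes.
- The interval L from consent to surgery is the same for all patients. The protocol does not give it, so 0 to 3 months is shown.

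**Reproducing the protocol's own figures.** Sample size: 14 degrees of freedom × 10 = 140, plus 14 = 154. Accrual rate: (80 + 100) × 0.70 / 12 = 10.5 patients per month. Duration: 154 / 10.5 = 14.7 months, against 15 stated. Both agree.

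**Patients already disclosed when the last patient enrols.** A patient is disclosed L + 6 months after consent, so the number is (14.67 − 6 − L) × 10.5.

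| L (months) | Calculation | Patients disclosed |
|---|---|---|
| 0 | 8.67 × 10.5 | 91 |
| 1 | 7.67 × 10.5 | 81 |
| 2 | 6.67 × 10.5 | 70 |
| 3 | 5.67 × 10.5 | 60 |

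**Six-week assessments after the first disclosure.** The first disclosure falls at month 6 + L. A patient enrolled at month t has the six-week test at t + L + 1.38, which is later than the first disclosure when t exceeds 6 − 1.38 = 4.62. Patients enrolled before that: 4.62 × 10.5 = 48.5. The remainder is 154 − 48.5 = 105.5, reported as about 105, or 68% of 154. L cancels because it is taken as the same for everyone. If it varied between patients, the count would shift.

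**With release only at database lock,** the number of six-week assessments that follow a disclosure is 0, and the sample size stays at 154.

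**Reading 6.2 against 10.1.** Section 6.2 locks one particular form to researchers. Section 10.1 grants directly involved members access to what is in Castor, mentions roles, and does not refer to the lock. The two can be read together, with the specific rule governing, but section 10.1 does not say so. Section 10.1 also opens a second route: the team extracts data from the patient record, and that is where section 6.2 has the injury written after each patient's last evaluation.

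**The case against.** The strongest reply is that no outcome is measured after that same patient's injury has been disclosed. The primary assessment is at 6 weeks, the last at 6 months, and the form is opened only afterwards. This is correct, and it is why the risk is indirect.

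The tests also leave limited room for assessor influence. Under section 5.1 the blinded patient points to one of five descriptors, with strips in randomised order. Section 5.4 uses a forced-choice staircase, and much of the remainder is patient questionnaires. This reduces the first risk without removing it, and it does nothing about analysis choices.

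Section 6.2 names the outcome assessor, the researchers and the investigator separately, so they may be different people. That is possible, but the protocol does not require it.

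Three stronger readings are tempting, and the protocol does not support them:
- **A reader might infer that section 10.1 opens the injury data to the whole team, so that there is no assessor blind.** Its sentence mainly keeps outsiders out, the same section assigns roles, and the specific lock in 6.2 can be taken to govern. What remains is a missing exception.
- **A reader might infer that staff can work out the category of patients still under test from each surgeon's habits.** The protocol gives no number of surgeons and no surgeon-level pattern, and does not say that assessors know who operated. With no randomisation there is no allocation sequence to deduce either.
- **A reader might infer that the team reviews accumulating results by injury group.** Access is possible, but no such review is planned and section 8.4 rules out interim analyses.

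Finally, the counts above describe the overlap between disclosure and testing. They do not count compromised assessments.

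**Conclusion.** The point holds in a limited form. The protocol fixes a release rule that works patient by patient, calls the study double-blind, and has no rule that keeps the injury data closed until the end. Those who test, prepare data or analyse are not kept apart from the person who unblinds, so injury and taste outcome can be linked on a growing set of finished patients.

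About 60 to 91 patients would be disclosed when the last one enrols, for an assumed consent-to-surgery interval of 3 to 0 months. About 105 of 154 six-week assessments would follow the first disclosure. Slower disclosure after the last visit, or withdrawals, would lower these figures.

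The size of any resulting bias cannot be derived from the protocol. The risk is modest and avoidable, and it is worth correcting because the remedy is cheap. Section 10.1 needs alignment with 6.2; it is not evidence that the blind is absent.

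**What to change.** In section 6.2:
- State that the CTN injury item stays hidden from everyone who tests patients, prepares the data or analyses them until the last patient's final visit and database lock.
- Have the surgeon, who already knows the category, make the patient-record entry after that patient's last evaluation, in place of the investigator.
- Bar assessors and analysts from that entry until lock, including while data are being extracted from the record. Without this, moving the entry to the surgeon would leave the record route open.

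In section 10.1, add to the Castor access sentence an exception for the surgeon's CTN injury form, closed until database lock.

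Patients can still learn their injury type after their own last visit. The sample size and visit schedule do not change. The cost is a Castor role setting, wording in two sections, and a few minutes of surgeon time per patient.
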